## Abstract

**Background:**

Opioid agonist treatment (OAT) for patients with opioid use disorder (OUD) has a convincing evidence base, although variable retention rates suggest that it may not be beneficial for all. One of the options to include more patients is the introduction of heroin-assisted treatment (HAT), which involves the prescribing of pharmaceutical heroin in a clinical supervised setting. Clinical trials suggest that HAT positively affects illicit drug use, criminal behavior, quality of life, and health. The results are less clear for longer-term outcomes such as mortality, level of function and social integration. This protocol describes a longitudinal evaluation of the introduction of HAT into the OAT services in Norway over a 5-year period. The main aim of the project is to study the individual, organizational and societal effects of implementing HAT in the specialized healthcare services for OUD.

**Methods:**

The project adopts a multidisciplinary approach, where the primary cohort for analysis will consist of approximately 250 patients in Norway, observed during the period of 2022–2026. Cohorts for comparative analysis will include all HAT-patients in Denmark from 2010 to 2022 (*N* = 500) and all Norwegian patients in conventional OAT (*N* = 8300). Data comes from individual in-depth and semi-structured interviews, self-report questionnaires, clinical records, and national registries, collected at several time points throughout patients’ courses of treatment. Qualitative analyses will use a flexible inductive thematic approach. Quantitative analyses will employ a wide array of methods including bi-variate parametric and non-parametric tests, and various forms of multivariate modeling.

**Discussion:**

The project’s primary strength lies in its comprehensive and longitudinal approach. It has the potential to reveal new insights on whether pharmaceutical heroin should be an integral part of integrated conventional OAT services to individually tailor treatments for patients with OUD. This could affect considerations about drug treatment even beyond HAT-specific topics, where an expanded understanding of why some do not succeed with conventional OAT will strengthen the knowledge base for drug treatment in general. Results will be disseminated to the scientific community, clinicians, and policy makers.

**Trial registration:**

The study was approved by the Norwegian Regional Committee for Medical and Health Research Ethics (REK), ref.nr.:195733.

## Background

Opioid use disorder (OUD) is a major global health concern with an estimated caseload of 31.5 million in 2022 [1]. It is frequently related to infectious diseases from injection-based drug use, psychiatric disorders, deterioration of social relations, reduced workforce participation, and a tenfold increase in crude all-cause rate of mortality [2]. The treatment and care for patients with OUD has gradually developed from an initial emphasis on abstinence and withdrawal management, to regular prescriptions of opioid agonists for maintenance treatment (OAT) [3].

Half a century after the first initiatives of prescribing methadone for OUD in a regular manner [4, 5] OAT now has a strong evidence-base [6]. Overall, it contributes to a substantial reduction in mortality, general health benefits, and reduced use of illicit drugs and criminal activity [6–9]. Still, not all individuals find conventional OAT sufficiently attractive over time, and cycles of dropout and re-entering are ongoing challenges in these programs [10–12]. A variable retention rate of 20–84% has been observed [13]. Among the efforts to improve the inclusion of patients in OAT is the introduction of more diverse medication options, such as rapid-onset, short-acting injectable pharmaceutical opioids such as heroin [14].

The use of medical grade heroin (diacetylmorphine) in treating OUD has been applied in England since the 1920s, originally as hand-out prescriptions to take home [15, 16]. Initiatives to incorporate it into more regular OAT started in Switzerland in 1994, with promising results [17, 18]. Now, three decades later and after clinical trials from several European countries and Canada, the body of research suggests that heroin-assisted treatment (HAT) is beneficial for a sub-selection of patients in regard to health outcomes and reductions in use of illicit drugs and criminal behavior [19–21]. The results are less clear for longer-term outcomes such as mortality [6, 19].

Still, HAT remains politically controversial [22], and reduced illicit heroin use and criminal behavior may not be compelling arguments for its efficacy. Rather, as for any other medical treatment its impact may better be assessed by patients’ improvement in quality of life, everyday level of function, and mortality [23].

Although newer studies suggests that take home doses are a feasible and safe alternative for patients deemed suitable [24, 25], medical heroin is typically administered under rigorous and comprehensive medical supervision due to the risk of serious adverse events and diversion [26]. Studies on cost effectiveness suggest both excessive expenses and inconclusive results when compared with methadone treatment, which are possibly dependent on methodological issues and poor consideration of the mechanisms involved [20, 27, 28].

Additionally, most of the research on the effectiveness of HAT originates from randomized clinical trials which may have limitations concerning the understanding of long-term outcomes and the mechanisms behind [23]. Thus, the main contribution of HAT may lie in the engagement of a high-risk population in utilization of health- and social services over time, like the more conventional options of OAT [23, 29]. A more comprehensive view of outcomes beyond the mere quantity and frequency of drug use and criminal behaviour can provide crucial information about the mechanisms responsible for treatment effectiveness, and its possible impact on other clinically and socially relevant parameters [30].

The current Norwegian HAT study is presented in this context. The study is part of a clinical project by the Norwegian Directorate of Health, with the aim to evaluate the implementation of HAT into the national OAT services. It is based on a model from Denmark where the use of medical heroin was introduced in 2010, following the British “RIOTT” line of test trials from 2005 [31]. Denmark currently has five clinics as permanent parts of the national healthcare system, although a limited amount of research has been published from this model [32].

### The Norwegian HAT-project

OAT programs based on prescription of methadone and buprenorphine has in various forms been integrated into the Norwegian health and social services-system since 1997 [33]. In the spring of 2020, the Norwegian Directorate of Health introduced a time-limited, clinically based project on the use of pharmaceutical heroin in the specialist healthcare services. Based on a day-center model, treatment is offered at two designated clinics in the largest Norwegian cities of Oslo and Bergen. The clinics consist of injection sites and medical personnel for the administration of pharmaceutical heroin twice a day, in combination with a take-home oral overnight dose of slow-releasing opioid-agonist such as methadone or morphine. Take-home doses of heroin are not granted, and patients must attend daily all year around. Psychosocial services and support are also offered [34]. Patients are referred from other services of substance use disorder treatment, specialist healthcare services or general practitioners. Criteria for admission are ongoing OUD with at least one former attempt of conventional OAT, being over 18 years of age and with general competency of consent. Exclusion criteria are severe mental disorders with reduced competency of consent, pregnancy, or repeated violent behavior.

The Norwegian Centre for Addiction Research (SERAF) at the University of Oslo was granted the research-based evaluation of the HAT project in 2021. The study will be conducted together with Section for Clinical Addiction Research (RusForsk) at Oslo University Hospital, Bergen Addiction Research Group (BAR) at Haukeland University Hospital in Bergen, Centre for Alcohol and Drug Research (CRF) at Aarhus University in Denmark, and the Norwegian user organization proLARNett.

### Study aims

The primary aim of the research project is to examine the effects from implementing HAT in Norway for individual patients and for the health services organization. A secondary aim is to compare these findings with the Danish HAT program.

Based on the Norwegian Directorate of Health’s specifications in the project proposal, the study will cover the following thematic areas:

Explore the attitudes, experiences and challenges of HAT as perceived by patients, their relatives, and clinical staff.Describe changes in mental and physical health among patients receiving HAT, and in what way it is associated with outcomes such as quality of life, utilization of health- and social services, social reintegration, criminal behavior and use of illicit drugs.Report any serious adverse events and incidents at treatment initiation, during treatment, and after discharge from HAT.Perform an economic evaluation of the program with associated clinical benefits and societal costs.Evaluate the organizational processes involved in the implementation of HAT in Norwegian specialist healthcare services, and the eventual impact from HAT on OUD patients’ utilization of conventional OAT.Additional research relevant to HAT that is not explicitly outlined in the proposal (may require additional approvals from the Norwegian Regional Committee for Medical and Health Research Ethics.)

The themes were operationalized into six work packages, with corresponding research questions and data sources (shown in Table 1).

**Table 1 Tab1:** Overview of work packages

	Work package	Data source	Research questions
1	Attitudes and experiences of HAT	In-depth and semi-structured interviews with patients, family members and staff	What are the patients’ and staff’s experiences and views of HAT? What may be the effective and ineffective elements of HAT? What are the patients’ uses of other health and social services when in HAT? What are the patients’ preferences and views of medications in HAT?
2	Health, social, and treatment outcomes	Questionnaires Clinical records Registries	Does HAT affect patients’ physical and mental health over time? Does HAT affect use of health and social services and quality of life? Does HAT affect the use of health and social services? Does HAT affect criminal activities? Does HAT affect illicit drug use?
3	Serious adverse events	Clinical records	Does HAT affect frequencies of serious adverse events and overdoses among patients? How do these events differ from those among patients in standard OAT? What are the clinical circumstances and outcomes for serious adverse events that occur in the HAT clinic?
4	Cost-benefit evaluation	Clinical records Registries Key-account figures	What is the cost-effectiveness of HAT? Does HAT affect societal costs related to social benefits and crime? What is the cost of implementing HAT nationally in Norway?
5	Process evaluation	Interviews and questionnaires with patients, staff, and administrators	Are there critical organizational and structural elements of HAT? What are the barriers and success factors for implementing HAT in Norway? Is there a dynamic relationship in the flow of patients between HAT and standard OAT? Which patients are reached by HAT? How can HAT be implemented in the national health services?
6	Others	Additional data specified in further protocols	What are the pharmacological and subjective effects of heroin on patients, compared with other OAT medications?

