### Data sources

Data on the primary cohort of Norwegian HAT patients will be based on a prospective collection of both qualitative and quantitative variables from treatment inclusion and throughout the project period. For the cohorts of Danish patients, of Norwegian patients that have been referred to but not granted HAT, and of Norwegian patients in conventional OAT, data are mainly based on national registries.

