### Clinical records

Information will also be obtained from the individual patient’s routine clinical records on variables such as main vital signs, nutritional status, cognitive function and mental health, medication, and comorbidities, as well as more HAT-specific variables such as adverse events, dosage, and administration routes of the pharmaceutical heroin.

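### Work package 3 names clinical records as its only source but compares serious adverse events with OAT patients known mainly from registries, so true differences would be mixed with differing event capture

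*Protocol article*

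**What the plan says.** The third aim under Study aims is "Report any serious adverse events and incidents at treatment initiation, during treatment, and after discharge from HAT". Table 1 turns this into work package 3, with three questions. The first is "Does HAT affect frequencies of serious adverse events and overdoses among patients". The second is "How do these events differ from those among patients in standard OAT". The third concerns the circumstances and outcomes of events inside the HAT clinic.

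The table entry for the package and its source reads "Serious adverse events Clinical records". Work packages 2 and 4 in the same table list registries as well as clinical records.

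Three other sections bear on this:

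- **Clinical records** says the records supply routine health variables "as well as more HAT-specific variables such as adverse events, dosage, and administration routes of the pharmaceutical heroin".
- **Data sources** describes the Norwegian HAT cohort as followed by "prospective collection of both qualitative and quantitative variables from treatment inclusion and throughout the project period". For the Danish patients, the applicants not granted HAT, and the cohort "of Norwegian patients in conventional OAT, data are mainly based on national registries".
- **Central register databases** (with Table 2) commits the project to national registers for the cohorts, among them the Norwegian Patient Register and the Norwegian Cause of Death Registry. It does not tie them to work package 3.

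**The concern.** HAT patients attend every day and inject where medical staff are present. Nothing in the article describes similar observation of the roughly 8300 conventional OAT patients. An overdose handled in the HAT clinic can be expected in its records. A similar event in an OAT patient enters the data only if it reaches a register or another source. That pushes the comparison against HAT.

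The opposite push is also possible. A HAT patient's event away from the clinic or after discharge may never enter the clinical record, although the third aim covers events after discharge.

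This is the project's explicit safety comparison between HAT and conventional OAT. A larger cohort would not help, because unequal capture is a bias and not sampling error. The limitations in the Discussion cover causal isolation, self-report bias, representativeness and generalizability, but not differing event capture between cohorts.

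**Working it through.** The article states no event rate, effect size or power for this comparison, so there is no figure to reproduce. The check is first textual, then illustrative.

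**Step 1: the text side by side**

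| Item | What the article fixes | Where |
|---|---|---|
| Work package 3 questions | Effect of HAT on event frequency; difference from standard OAT; circumstances of in-clinic events | Table 1 |
| Work package 3 source | Clinical records only | Table 1 |
| Work packages 2 and 4 sources | Clinical records and registries, among others | Table 1 |
| Adverse events in clinical records | A HAT-specific variable | Clinical records |
| OAT and refused-applicant data | Mainly registries | Data sources |
| Event window | Initiation, treatment, after discharge | Study aims |

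Table 1 names registries where they are meant, so their absence from work package 3 is a stated source and not detail left to a fuller document. Only the third question is confined to the HAT clinic. The first two need a source that works in both groups and beyond the clinic.

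**Step 2: effect on a ratio (capture values are assumptions)**

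Apparent ratio = true ratio × (capture in HAT ÷ capture in OAT). With a true ratio of 1:

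- HAT 90%, OAT 75%: 0.90/0.75 = 1.20
- HAT 90%, OAT 60%: 0.90/0.60 = 1.50
- HAT 90%, OAT 45%: 0.90/0.45 = 2.00
- HAT 60%, OAT 90%: 0.60/0.90 = 0.67

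If a share d of HAT events falls after discharge and is missed, with OAT complete, the apparent ratio is 1 − d: 0.90, 0.75 and 0.60 for d = 10%, 25% and 40%.

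**Step 3: chance of a false difference (also assumed values)**

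Inputs from Study populations and size: 250 HAT and about 8300 OAT patients. Assumed: a simple comparison of two proportions, two-sided 5%, equal true risk of 10%.

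Formula: Φ[(|p1 − p2| − 1.96·SE0)/SE1], with SE0 from the pooled proportion and SE1 from the separate ones.

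For 90% against 60% capture:

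- p1 = 0.09 and p2 = 0.06
- Pooled proportion = (22.5 + 498)/8550 = 0.0609
- SE0 = √[0.0609 × 0.9391 × (1/250 + 1/8300)] = 0.01535
- SE1 = √[0.09 × 0.91/250 + 0.06 × 0.94/8300] = 0.01829
- Result: Φ[(0.0300 − 0.0301)/0.01829] ≈ 0.50

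| Capture HAT / OAT | Apparent ratio | True risk 5% | 10% | 20% |
|---|---|---|---|---|
| 90% / 75% | 1.20 | 11% | 16% | 27% |
| 90% / 60% | 1.50 | 31% | 50% | 78% |
| 90% / 45% | 2.00 | 61% | 85% | 99% |
| 60% / 90% | 0.67 | 16% | 35% | 71% |

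**Step 4: does a shared register remove the bias?**

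Only if the register catches the same share in both groups. If a share m of serious HAT events is managed on site and never reaches a register, while OAT events are caught in full, the apparent ratio is 1 − m. That is again 0.90, 0.75 or 0.60 for m = 10%, 25% or 40%. Dropping on-site events without a further check could therefore favour HAT.

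**The case against.** The strongest reply is that one cell of an overview table is not the whole data plan. The project commits to national registers for all cohorts, including those for hospital care and cause of death, and the Discussion says records, self-report and register data will be combined. The article does not limit clinical records to the HAT clinic or to time in treatment. HAT data are collected throughout the project, and staff complete a questionnaire when a patient leaves. OAT data come mainly, not solely, from registries, and Table 1 does not say whose clinical records it means. Clinical records are the right source for the question about in-clinic events. The Discussion also promises cautious interpretation.

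Much of this stands, and it rules out several stronger readings:

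- A reader might infer that the comparison measures nothing but recording practice. The text supports only that true differences and capture differences would be mixed.
- A reader might infer that events after discharge are lost. Deaths and hospital-treated events after discharge are reachable through registers already planned. What holds is that the single source named for this package does not clearly deliver them.
- A reader might infer that time at risk differs between the groups. The article defines it for neither, and an article may leave that to the full protocol or analysis plan.
- A reader might take a ratio such as 2.0 as the expected bias. No capture figure is given, so every ratio here is illustration.

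The reply does not remove the core. Planning registers for the project is not the same as assigning them to this package, and general caution about causal inference does not address unequal event capture.

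**Conclusion.** The point holds as a mismatch between the question asked and the source assigned to it. Read together, Table 1, Data sources and Clinical records set HAT events from clinical records against OAT events found mainly in registers. A difference in serious adverse events or overdoses could then be real, an effect of capture, or both.

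The bias may run either way and its size cannot be set from the document. The ratios from 0.60 to 2.00, and the false-difference chances from 11% to 99% in the table, rest on assumed capture and risk and show only that moderate differences in capture would matter.

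The conclusion also rests on one inference: that the clinical records meant are those of HAT patients. The sections on data sources and clinical records support this, but Table 1 does not say it. The matter should be settled before the comparison is run.

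**What to change.** Reconcile Table 1 with Study aims, Data sources and Central register databases:

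1. Change the work package 3 source to clinical records and registries.
2. Base the comparison of HAT with conventional OAT, and with refused applicants, on deaths and hospital-treated events, including overdoses. Take these from the Norwegian Patient Register and the Norwegian Cause of Death Registry in all groups, with identical definitions and follow-up, including time after leaving HAT.
3. Report clinic-recorded on-site events separately and descriptively for HAT.
4. Add a sensitivity analysis that also counts on-site serious events and overdoses on the HAT side, counting once any event found in both sources.
5. State as a limitation that on-site management may keep HAT events out of the registers, so shared registers do not guarantee equal capture.

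The cost is one table entry and some analysis wording, since the registers are already listed in Table 2. The downside is that on-site events that never reach a register leave the main comparison. This could favour HAT, which is why the sensitivity analysis is needed. That analysis can err the other way, because OAT events outside the registers stay uncounted, so the two results should be shown together.

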## Methods and design

The project is a multi-dimensional study, involving an array of methodological approaches and data sources. The main part is a prospective cohort study of all Norwegian HAT patients, compared with the cohorts of all Danish HAT patients and Norwegian patients in conventional OAT.

### Study populations and size

The primary target group is all patients enrolled in the two HAT clinics in Oslo and Bergen during the period 2022–2026, with an expected total sample size of *N* = 250. Based on earlier findings, the ratio of men to women is expected to be 4:1, with an age distribution of 27–60, presenting multiple substance use disorders. As the study is based on the total clinical population, representation will be determined by its demographics, with no exclusion of genders or ethnic minorities. The patients who have applied to but have not been accepted for HAT will be used for comparison, with an expected sample size of 100.

Comparative data from the Danish cohort will be drawn from the comprehensive dataset at Aarhus University from 2010 and onwards, with a sample size of approximately 500 [35]. Likewise, the comprehensive dataset at SERAF on the cohort of Norwegian patients in conventional OAT from 2003 has an approximate sample size of 8300.

### Data sources

Data on the primary cohort of Norwegian HAT patients will be based on a prospective collection of both qualitative and quantitative variables from treatment inclusion and throughout the project period. For the cohorts of Danish patients, of Norwegian patients that have been referred to but not granted HAT, and of Norwegian patients in conventional OAT, data are mainly based on national registries.

### In-depth and semi-structured interviews and observation

The qualitative part of the project includes individual in-depth and semi-structured interviews with patients and relatives on their views and experiences with HAT, and focus group interviews with staff concerning implementation, clinical and legal aspects of the project. Semi-structured interview protocols have been developed by the project group and user representatives. Interviews will include 25–35 patients and 10–20 family members, conducted by a team of researchers and user representatives at 1, 6, 18 months after patients enter treatment, and with relatives after 4 and 12 months. Focus group interviews with staff will be conducted at 3, 9 and 18 months. Further, the clinic managers are being interviewed at several timepoints from the planning of the clinics and throughout the duration of the project.

For insights into clinic aspects not identified through interviews, researchers will conduct participant observation in the clinics over several periods of 1–2 weeks throughout the study.

